## Methods

### Overall aim

The overall aim of the project is to study whether a preparatory online value clarification tool decreases decisional conflict in patients who are considering participation in early phase clinical trials, by improving patient-physician communication with respect to the discussion of patients’ preferences and the decision making process. Following the Medical Research Council – UK – guideline for complex interventions [22], the study consists of two major parts that take place simultaneously, as illustrated in Fig. 1:
the development and feasibility testing of the OnVaCT (phase 1 and 2 of MRC framework);the implementation and evaluation of the OnVaCT (phase 3 and 4 of MRC framework).

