### Part 2: implementation and evaluation of the OnVaCT

#### Aims

To evaluate the effect of implementation of the OnVaCT with accompanying training on:
patients’ decisional conflict (primary outcome);patient-physician communication regarding the discussion of patients’ preferences and the decision making process (secondary outcome).To investigate the actual usage of the OnVaCT (secondary outcome).

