#### Procedures

##### Implementation phase

When the members of the project team agree on the content of the OnVaCT, we will develop a training session for the medical oncologists of the early phase clinical research units. All members of the study teams will be informed about the forthcoming implementation of the tool and trained how to handle the preparatory work of the patient by using the tool and how to integrate patients’ values and preferences and further information needs in the communication with patients facing a choice whether or not to participate in an early phase clinical trial. We will use the barriers as perceived by caregivers of the team as explored during the development of the OnVaCT as input for the development of the accompanying training module. The module will be developed in close collaboration with a psychologist with educational experience, and based on previously developed training modules in e.g. the VOICE study, in which clinicians were trained in exploring patients’ preferences and how to use a preparatory tool during consultations [30], and the CHOICE trial, in which a training was developed on shared decision making in consultations about palliative care, specifically for oncologists [31].

Directly after the training, the OnVaCT will be implemented in clinical practice, and the post-test will start. Patients in the post-test will use the tool in preparation of their first visit to a medical oncologists regarding early phase clinical trials.

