#### Measurements

Table 2 gives an overview of the baseline and outcome measurements in part 2 of the OnVaCT project.

**Table 2 Tab2:** Measurements in part 2 of the OnVaCT project

Outcome	Instrument	Source
Baseline measurements		
Patient’s health literacy	Set of Brief Screening Questions (SBSQ-D): Dutch version [32, 33] of the 3-item health literacy scale of Chew et al. [30] on 5-point Likert scales.	Questionnaire at T1
Sense of hope	Herth Hope Index (HHI) [34, 35]: Items on a 4-point Likert scale on three dimensions: temporality and future, positive readiness and expectancy, and interconnectedness.	Questionnaire at T1
Technology acceptance	Measurements from the Technology Acceptance Model (TAM), adapted in the Unified Theory of Acceptance and Use of Technology (UTAUT) [36–38]. In total, 15 items on a 7-point Likert scale are included.	Questionnaire at T1, only in post-test
Satisfaction with the tool	Website Satisfaction Scale [39–42]: A Dutch version of the Website Satisfaction Scale will be used, consisting of the subscales ‘satisfaction with comprehensibility’ (3 items), ‘satisfaction with attractiveness’ (5 items) and ‘satisfaction with emotional support’ (4 items), all on a 7-point Likert scale.	Questionnaire at T1, only in post-test
Quality of life	QLQ-C30 version 3.0 [43] of the European Organisation for Research and Treatment of Cancer (EORTC): 28 items on a 4-point Likert scale and 2 items on a 7-point Likert scale.	Questionnaire at T1
Primary outcome		
Decisional conflict	Decisional Conflict Scale (DCS) [25]: 16 items on a 5-point Likert scale from 0 to 4. The items are summed, divided by 16 and multiplied by 25 to get a total score for decisional conflict on a 0–100 scale.	Questionnaire at T3
Secondary outcomes		
Extent to which caregivers involve patients in shared decision-making	Adapted Observer OPTION^MCC^ [44] based on the OPTION^5^ [45]: in each recorded consultation, 7 behavioural competences for the medical oncologists regarding goal talk (1 item), option talk (2 items), team talk (1 item), decision talk (2 items) and evaluation talk (1 item) will be coded on a 5-point Likert Scale (0 = ‘the behaviour is not observed’ – 4 = ‘the behaviour is observed and executed to a high standard’). Following OPTION^5^ guidelines, these scores will be transformed to a 0–100 score.	Analysis of recorded consultation

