#### Statistical analysis

All analyses regarding the evaluation of the OnVaCT will be performed in the most recent version of IBM SSPS Statistics. Descriptive statistics and frequency distributions will be generated for the patients’ demographics and medical disease characteristics. For the analysis of the main and secondary outcome measures, an intention-to-treat analysis will be used, thereby including patients who were included in the post-test group (i.e. after the implementation of the OnVaCT with accompanying training) regardless of whether or not they used the OnVaCT.

For the analysis of decisional conflict, a one-sided t-test will be performed between the pre- and post-test measurements. Patient demographics, performance status, health literacy and the level hope may be used as covariates to correct for possible imbalance between the patients from the two study periods (pre-test and post-test) by means of regression analysis. In addition, a mediation analysis will be performed using Structural Equation Modelling (SEM) to calculate the direct effect of the use of the OnVaCT on decisional conflict and to what extent that effect was mediated by communication during the consultation (i.e. the extent to which patients are involved in the decision making process as measured with the adapted Observer OPTION^MCC^ [44]; and the extent to which patient values and preferences are discussed as measured with a codebook we will develop). In the SEM analysis, patient demographics, performance status, health literacy, the sense of hope and the quality of life at baseline may be used as covariates to correct for possible imbalance between the patients from the two study periods (pre- and post-test).

Secondary outcomes, e.g. the total score for the shared decision making process during consultation, the discussion of patients’ values and preferences by patients, relatives and caregivers and the length of the consultation will be compared between the two test periods using two-sided t-tests. Again, the regression analysis may be used to correct for possible differences in patient demographics, performance status, health literacy and hope between the patients from the two study periods (pre- and post-test). Descriptive statistics will be generated for technology acceptance and satisfaction with the tool, which are only measured in the post-test.

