The OnVaCT study uses both qualitative and quantitative research methods to develop and perform the initial testing phase for a value clarification tool that is meaningful for both patients and oncologists. This mixed-methods approach offers the opportunity to build on in-depth analyses to gain a better understanding of the underlying processes of difficult and potentially life-changing choices to create an OnVaCT that suits patients’ decision making processes, but also to quantitatively evaluate the OnVaCT. The OnVaCT (with training module) will already be implemented in clinical practice during the evaluation of the tool in the three largest centres for early phase clinical research in the Netherlands (located in Rotterdam, Utrecht, and Amsterdam), making it easy to continue using the OnVaCT when it appears to be of value during the evaluation. Additionally, studies regarding other (end-of-life) decisions, which may pose a similar type of decision conflict, may also benefit from the results of the current project. Even though the benefit from treatment may be known, and therefore more precise arguments pro and contra treatment can be made, patients who are able to identify and realize their personal values regarding these treatments, could still benefit from less decisional conflict and more attuned discussions with their oncologists regarding the choices they make.

If this project has its hypothesized positive outcome, meaning that decisional conflict indeed seems to decrease by using the OnVaCT, the project can be followed up in different manners. For instance, regional hospitals could be asked to participate and use the OnVaCT to aid in decision making after “bad news” has been delivered on the absence of regular treatment options, which could help improve specific referral for early phase clinical trials. As the use of the OnVaCT in peripheral hospitals provides all eligible patients to consider their preferences regarding participation in early phase clinical trials, patients who come to the conclusion that participation is not suitable for them, do not have to be referred to an early phase clinical research unit at all. As only a specific selection of patients who actually consider participating in early phase clinical trials will be referred, the medical oncologists could perhaps attune their consultations even better at this particular population.

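### The mediation model, the overall aim and the expected conclusion credit the tool or its use, but the design can estimate only the joint effect of tool plus oncologist training

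*Protocol article*

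**What the plan says.** The protocol article names the effect of interest in two ways.

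**As a package.** The Part 2 aims open with "To evaluate the effect of implementation of the OnVaCT with accompanying training on" decisional conflict and communication. The Statistical analysis section describes the post-test group as following implementation of both tool and training, and keeps post-test patients in the analysis whether or not they used the tool. The Discussion also describes tool and training module as one package.

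**As the tool or its use.** The overall aim is to study "whether a preparatory online value clarification tool decreases decisional conflict". The mediation analysis is meant "to calculate the direct effect of the use of the OnVaCT on decisional conflict", and to show how much of that effect runs through communication in the consultation. The Discussion describes the hoped-for positive outcome as "meaning that decisional conflict indeed seems to decrease by using the OnVaCT".

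Three further statements matter:
- On timing, the Implementation phase section says: "Directly after the training, the OnVaCT will be implemented in clinical practice, and the post-test will start".
- On content, the same section says the training covers "how to integrate patients’ values and preferences and further information needs in the communication with patients".
- On the mediator, Table 2 says the adapted Observer OPTION-MCC scores "7 behavioural competences for the medical oncologists".

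**The concern.** Two interventions begin at the same moment in every post-test period. One acts on the patient (the tool) and one on the oncologist (the training). A pre/post comparison estimates what they do together. If the result is then reported as the effect of the tool, or of using it, the report answers a question that the data cannot address.

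The mediation analysis suffers most. It is presented as showing how the tool works, namely by improving communication. But the main communication measure rates the oncologist, and the oncologist has just been trained in communication. A gain on that measure could come from the training, from the tool, or from both.

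A second, smaller problem lies in the word use. Elsewhere in the same section it means that a patient actually used the tool, and actual usage is tracked as a secondary outcome. An analyst could therefore take the model's exposure to be individual use. That would place post-test non-users, who still saw trained oncologists, in the comparator, and would contrast self-selected users with everyone else.

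**Working it through.** **1. The plan's own figure.** The sample size section gives an effect size of 0.30, one-sided alpha of 0.05 and 80% power. The number per period is 2 × (1.645 + 0.842)² / 0.30² = 137.4, rounded up to 138, so 276 in total. This reproduces the stated number. With the assumed SD of 12, an effect size of 0.30 is 0.30 × 12 = 3.6 points on the 0–100 scale.

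**2. Which contrasts exist.**

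| Period | Tool | Training |
|---|---|---|
| Pre-test | no | no |
| Post-test | yes (offered) | yes |

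No period has one component without the other. Patient covariates cannot separate the two, because every post-test patient is seen after the oncologists were trained.

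**3. What this does to the mediated path.** Let the post-test period raise the mediator by *a* = *a*(tool) + *a*(training), and let *b* be the slope of decisional conflict on the mediator. With period as the exposure, the indirect effect is *a* × *b*, which depends only on the sum. The values below are assumptions for illustration and do not come from the documents: *a* = 0.6 SD, *b* = -0.5, outcome SD 1 within period.

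| *a*(tool) | *a*(training) | Estimated indirect effect | Part due to tool |
|---|---|---|---|
| 0.6 | 0 | 0.6 × (-0.5) = -0.30 | -0.30 |
| 0.3 | 0.3 | -0.30 | -0.15 |
| 0 | 0.6 | -0.30 | 0 |

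The estimate is the same in all three rows, while the tool's share runs from all of it to none. A simulation of the last row gave an indirect effect of about -0.30 and a direct effect of about 0. In that row a pure training effect, as large as the one the trial is powered for, would be labelled a tool effect mediated by communication.

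**4. Coding actual use instead.** Suppose a share *u* of post-test patients use the tool, use is unrelated to the mediator and outcome, and the periods are of equal size. Users have a mediator mean of *a*. Non-users pooled with pre-test patients have *a*(1 - *u*)/(2 - *u*). The difference is *a*/(2 - *u*). With the tool doing nothing (*a* = 0.6, all from training):
- *u* = 0.8: 0.6 / 1.2 = 0.50, indirect effect 0.50 × (-0.5) = -0.25 (simulated -0.251)
- *u* = 0.6: 0.6 / 1.4 = 0.43, indirect effect 0.43 × (-0.5) = -0.21 (simulated -0.213)

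The uptake values are assumptions, as the documents give none. Coding by use shrinks the estimate but still shows an effect for an inert tool. Neither coding separates tool from training.

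**5. Which coding the text implies.** The Statistical analysis section fixes intention-to-treat for the main and secondary outcomes. It justifies the model's covariates by possible differences between patients of the two periods, which fits period as the exposure. It never states the coding of the exposure.

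**The case against.** The strongest reply is that this is shorthand. Training is named beside the tool many times, including in the intention-to-treat definition just before the mediation sentence, and the project is framed under guidance for complex interventions. Training that changes oncologist behaviour is part of the intended mechanism, so as a package effect the path is correctly included. If period is already the exposure, the fix changes no estimate.

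Much of this stands. The training is not hidden, and the primary analysis is a comparison of periods. The shorthand defence is weaker for the mediation sentence. That sentence speaks of use, a word the section has just applied to individual patients, and it states a mechanism that the data cannot assign to the tool. A package effect is a sound target, but the article should then call it that.

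A reader might infer two stronger points that the document does not support:
- **The intention-to-treat principle is broken.** That follows only if the model codes actual use. The article does not say so, and its reason for the covariates points to period. Any count of misplaced patients would also need an uptake figure, which is not given.
- **The tool will be rolled out to regional hospitals without training.** The Discussion only suggests that such hospitals could be asked to take part. It is silent on training there, and elsewhere in the same section the tool is described with its training module.

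**Conclusion.** The point holds as an inconsistency over what is being estimated. The overall aim, the mediation sentence and the anticipated conclusion attribute the effect to the tool or its use. The Part 2 aim, the intention-to-treat definition and the timing of implementation support only an effect of tool plus training. The tool's own effect is not identified, and the path through Observer OPTION-MCC may reflect training partly or wholly. The codebook mediator is less directly exposed, because it also counts what patients and relatives contribute, but its caregiver component has the same problem.

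The size cannot be fixed from the documents. The tool's share of the mediated effect could lie anywhere from none to all, and the -0.30, -0.25 and -0.21 SD figures rest on assumed values. Coding by actual use is a risk left open by the wording, not a stated plan.

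The primary t-test, the secondary comparisons by period and the sample size of 276 are unaffected. Calendar-time differences between the periods are a separate matter, which the article discusses among its limitations.

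**What to change.** Before the post-test data are analysed:
1. State that the exposure in the structural equation model is study period (pre-test or post-test) for all intention-to-treat patients.
2. Label the total, direct and mediated effects as effects of the package, tool plus oncologist training.
3. Bring the overall aim and the Discussion's statement of a positive outcome into line with the Part 2 aim.
4. Mark any analysis by actual use as exploratory and outside the intention-to-treat comparison.

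These are changes of wording and specification. They need no extra data and no change to the sample size. The cost is a narrower claim: a positive result would support the tool delivered with training, and would say nothing about the tool alone.

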#### Purposeful sampling

Based on research on the calculation of sample sizes for qualitative interviewing [25], purposeful sampling will require a total of 24 serial interviews with 12 patients (or less if saturation – i.e. the interviews no longer provide new insights – is reached). Knowing that a small number of oncologists are collaborating in the three participating early phase clinical research units, we will aim for 2–3 semi-structured interviews per unit (*n* = 6–8 in total).

The total number of patients, representatives and relatives participating in the patient focus group might fluctuate due to the natural courses of the diseases/treatments, but we aim for the focus group to contain 6–8 individuals with a range in patient characteristics. There will be three focus groups with medical oncologists (in training), each in one of the participating hospitals with an early phase clinical research unit and consisting of 3–4 oncologists.

The think aloud sessions for piloting of the value clarification tool will be conducted with patients (*n* = 8–10) and with medical oncologists (*n* = 6). Also healthy subjects and patient representative (s) will be asked to participate in this phase; the number of participants depends on the developmental process. The test sessions with healthy subjects, primarily take place for usability purposes, but may also reveal some additional insights regarding the (presentation of the) content of the tool, since they – like our target patient population – have no prior knowledge about the tool.

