#### Sample size calculation

The sample size calculation is based on decisional conflict as the primary outcome. Following literature, we assume a mean decisional conflict score of 27 (sd = 12) in the pre-implementation period [7]. To acquire an 80% power to detect an effect size of .30 with an alpha-level of .05 (one-sided), a total sample size of 276 patients is required (138 in the pre-test before the implementation of the OnVaCT and another 138 after the implementation). The three participating hospitals currently see approximately 400–500 new patients a year who consider participation in phase I clinical trials. Based on previous research, we expect a response rate of approximately 40%. We thus need approximately 12 months in the pre-test and another 12 months in the post-test to recruit the required number of patients. We will start the pre-test 18 months before the implementation of the OnVaCT, and if needed, we can spend another 18 months for the post-test. Hence, the inclusion of 276 participants based on the sample size calculation is feasible.

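### The planned tests treat patients as independent although a small number of trained oncologists see them; this is least tenable for the outcomes that score the oncologist's own consultation

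*Protocol article*

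**What the plan says.** The Statistical analysis section names a one-sided t-test of decisional conflict between the pre-test and post-test periods. It says that the secondary outcomes (the shared decision-making score, the discussion of values and the length of the consultation) "will be compared between the two test periods using two-sided t-tests". Regression may be used to correct for imbalance between the periods. The covariates listed are demographics, performance status, health literacy and hope; the SEM adds baseline quality of life. All are patient-level. No oncologist or hospital term appears.

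The Sample size calculation section sets out "To acquire an 80% power to detect an effect size of .30" at a one-sided 5% level, with "138 in the pre-test before the implementation of the OnVaCT and another 138 after the implementation". It mentions no correlation within oncologist or hospital.

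Three other places describe the clustering:
- Purposeful sampling (part 1): "Knowing that a small number of oncologists are collaborating in the three participating early phase clinical research units".
- Implementation phase: the oncologists of these units are trained between the two periods, as part of what is being evaluated.
- Table 2: the adapted Observer OPTION score rates seven behaviours of the oncologist in each recorded consultation. The values discussion is coded separately for patient, relatives and caregiver.

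The SEM uses the OPTION score and the values discussion as mediators of the effect on decisional conflict.

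**The concern.** Part of the intervention reaches patients through a few clinicians, each of whom will hold many recorded consultations. Consultations by the same oncologist are likely to resemble each other, most of all on a measure that rates that oncologist's behaviour. A t-test on patients ignores this.

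Two mechanisms pull in opposite directions. Differences between oncologists that stay the same over time cancel in a before-after comparison, so the t-test's standard error is too large. If oncologists change by different amounts after training, or their shares of patients shift between periods, that variation does not cancel and the standard error is too small. The trial's explanatory claim is that the tool lowers conflict by improving communication. It runs through the outcomes most exposed to this.

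**Working it through.** **1. The plan's own figure.** Inputs from the Sample size calculation section: effect size d = 0.30 (3.6 points at SD 12), one-sided alpha 0.05, power 80%, n = 138 per period.

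- n = 2 × ((1.645 + 0.842)/0.30)² = 137.4, rounded up to 138 per period, total 276.
- Power at 138 = Φ(0.30/√(2/138) − 1.645) = Φ(2.492 − 1.645) = 80.2% (80.0% with the noncentral t).

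The figure reproduces exactly for independent patients.

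**2. Assumptions that the article does not supply.**
- Number of oncologists, K: none is given for part 2. I take 12, the upper end of three part 1 focus groups of 3–4 oncologists, so m = 138/12 = 11.5 patients per oncologist per period.
- ρ, the correlation between patients of the same oncologist in the same period: 0.02–0.05 for patient-reported conflict, 0.2–0.3 for oncologist-scored behaviour.
- r, the correlation of an oncologist's effect between periods: 0.5 to 1.
- The same oncologists serve in both periods with equal shares of patients.

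**3. Formulas.**
- Design effect: DE = 1 + (m − 1)ρ − mρr.
- True type I error of the planned t-test: one-sided 1 − Φ(1.645/√DE); two-sided 2[1 − Φ(1.960/√DE)].
- Power of a test with the correct standard error: Φ(2.492/√DE − 1.645).
- Power of the planned t-test as it stands: Φ((2.492 − 1.645)/√DE).

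**4. Oncologist-scored outcomes, two-sided 5% t-test, K = 12.**

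| ρ | r | DE | True type I error |
|---|---|---|---|
| 0.2 | 1 | 1 + 2.10 − 2.30 = 0.80 | 2.8% |
| 0.2 | 0.8 | 1 + 2.10 − 1.84 = 1.26 | 8.1% |
| 0.3 | 1 | 1 + 3.15 − 3.45 = 0.70 | 1.9% |
| 0.3 | 0.8 | 1 + 3.15 − 2.76 = 1.39 | 9.6% |
| 0.3 | 0.5 | 1 + 3.15 − 1.725 = 2.425 | 20.8% |

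DE equals 1 when r = 1 − 1/m = 0.913. Below that value the t-test is anti-conservative, whatever ρ is.

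The last row depends on K: with 9 oncologists (m = 15.3) it becomes DE 3.00 and 25.8%; with 20 (m = 6.9), DE 1.735 and 13.7%. A simulation at K = 12 and ρ = 0.2 with balanced shares agreed with the formula: 3% at r = 1 and 8% at r = 0.8.

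**5. Shifting patient shares.** With r = 1, DE = (1 − ρ) + ρ(138/2)Σ(change in share)². As an example, let each of 12 oncologists' shares move by 5 percentage points, six up and six down. Then Σ = 12 × 0.05² = 0.03, and at ρ = 0.2, DE = 0.80 + 0.2 × 69 × 0.03 = 1.214. The type I error is 7.5%, even with perfectly stable oncologists.

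**6. Decisional conflict, one-sided 5% t-test, K = 12.**

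| ρ | r | DE | Type I error, planned test | Power, planned test | Power, valid clustered test |
|---|---|---|---|---|---|
| 0.02 | 1 | 0.980 | 4.8% | 80.4% | 80.9% |
| 0.02 | 0.8 | 1.026 | 5.2% | 79.9% | 79.3% |
| 0.05 | 0.8 | 1.065 | 5.5% | 79.4% | 77.9% |
| 0.05 | 0.5 | 1.2375 | 7.0% | 77.7% | 72.4% |

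The last column uses the normal approximation. With only 12 oncologists, small-sample degrees of freedom cost a little more: in a simulation of the bottom row, a paired analysis at oncologist level had 69% power.

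**The case against.** A reader might infer that the 80% power is wrong and that every planned standard error is too small. The documents support neither. The 80% reproduces exactly. It refers to decisional conflict alone, and no power is claimed for the communication outcomes. Every departure from it depends on ρ, r and K, none of which the article gives.

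The direction of the error is also open. Nothing in the article says how uniformly oncologists will respond to training, so differential response is possible but not documented. That the same oncologists serve in both periods is inferred from the design, and the count of 12 comes from planned focus-group attendance in part 1. Overlap between the periods is not itself harmful, because it is what lets stable oncologist differences cancel.

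Decisional conflict is reported by the patient three weeks after the consultation, often after a further contact with an oncologist or nurse practitioner, so a small ρ is plausible. What patients and relatives say about values is not simply the oncologist's behaviour. The article is also condensed: the full plan may specify the SEM's standard errors or the recording of an oncologist identifier.

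All of this stands and limits the point. It does not remove it. The t-tests and covariates are stated choices, and no stated adjustment addresses an outcome that rates the oncologist. If different oncologists served in the two periods, nothing would cancel (r = 0), and the inflation would be larger than in the tables.

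**Conclusion.** The point holds in limited form. Independence between patients is assumed without support, and the resulting error can go either way.

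- **OPTION score, consultation length and the caregiver's part of the values discussion.** This is where the matter is serious. Under the assumptions above, a nominal 5% test has a true level from about 2% to about 21%. The OPTION score and the values discussion carry the problem into the mediation model.
- **Decisional conflict.** The effect is probably smaller. The 80% is correct arithmetic on an unstated assumption: unsupported, not shown to be wrong.

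The size rests on assumed values of ρ, r and K, and on the inference that the same oncologists serve in both periods. The change should be made, but the primary comparison is not invalidated by this point.

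**What to change.** 1. Record which oncologist holds each T2 consultation.
2. Replace the t-tests and regressions with linear mixed models: fixed effects for period and hospital plus the chosen baseline covariates, random effects for oncologist and oncologist-by-period, and Satterthwaite or Kenward-Roger degrees of freedom. The oncologist-scored outcomes have priority.
3. Account for oncologist clustering in the SEM.
4. State that the 80% power assumes independent patients, and give it over a range of intra-oncologist and between-period correlations for the actual number of oncologists.

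The cost is one identifier per consultation, slightly more analysis work and a less favourable stated power. No extra patients are required.
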